### Measures

Table 2 shows the key measures used in the study, which are described below.

**Table 2 Tab2:** Summary of key measures

Outcome	Instrument	Frequency
Primary outcome (condensed hypothesis)		
Days of abstinence (greater abstinence among those with EMA, EMI, and EMA + EMI)	Self-report of any alcohol or drug use in last 90 days collected through Global Appraisal of Individual Needs Version 3 (GAIN-Q3) [53].	Baseline and 3 and 6 months after enrollment
	On-site urine drug screens for alcohol, amphetamine/methamphetamine, cannabis, cocaine/benzoylecgonine, and opiates/morphine	Baseline, twice in month 1, and 3 and 6 months after enrollment
Secondary outcomes		
HIV risk behaviors (fewer risk behaviors among those with EMA, EMI, and EMA + EMI)	Self-report of any risk behaviors (needle use, needle sharing, unprotected sex, multiple sexual partners, trading sex for drugs, victimization) in past 90 days collected through GAIN-Q3	Baseline and 3 and 6 months after enrollment
Other outcomes		
EMA and EMI use	Computer logs of EMA responses and EMI use (pages, minutes, interventions, engagement, patterns, comments, and so on)	Continuous

*EMA* Ecological Momentary Assessment, *EMI* Ecological Momentary Intervention

### GAIN-Q3

Researchers trained and supervised by [name] and [name] interview participants using the 25-min Global Appraisal of Individual Needs Quick Version 3 (GAIN-Q3) [53]. The GAIN-Q3 includes screeners with four to six questions on the recency of symptoms in nine problem areas (school, work, health, stress, HIV risk behaviors/victimization, internalizing disorders, externalizing disorders, substance use disorders, and crime/violence). These screeners were constructed to be correlated at .9 or more with the 11 to 43 symptoms in the full GAIN and cut points with approximately 90% sensitivity, specificity, and area under the curve compared with the full GAIN in the nine areas. Days-of-use measures have been validated against the timeline follow-back [65], collateral [66], records [67], and urine [66–68] and saliva tests [68]. The GAIN-Q3 also includes summary measures for health care utilization, functional impairment, quality of life, and life satisfaction.

### Urine drug screens

Interviews are supplemented with on-site urine screens. Urine will be tested on-site with CLIAA-waived QuikScreen cups using an immunochromatographic assay for rapid (2 to 5 min) qualitative results based on the Substance Abuse and Mental Health Service Authority (SAMHSA)-standard cutoffs for alcohol (20 mg/dl or 0.02% BAC), amphetamine/methamphetamine (1000 ng/ml), cannabis (50 ng/ml), cocaine/benzoylecgonine (300 ng/ml), and opiates/morphine (2000 ng/ml) [69].

### Measurement process/data collection

The team is implementing [70] follow-up procedures, which reliably produce over 90% follow-up rates across studies involving over 40,000 patients regardless of population for follow-up periods ranging from 3 months to 15 years. Steps include: (1) collecting contact information and Consent-to-be-contacted Forms and giving the participant an appointment card, (2) verifying participant contact information, (3) conducting outreach for past-due participants and discussing the situations at weekly research case review meetings, (4) mailing thank-you cards to participants, (5) scheduling follow-up appointments, (6) mailing 3- and 6-week post-enrollment flyers to participants and their collaterals, (7) implementing returned-mail procedures, (8) calling participants 6 weeks before 3- and 6-month research interview appointments to confirm date and location, (9) conducting outreach for unconfirmed cases and reviewing them at weekly meetings, (10) completing follow-up interviews and scheduling next appointments, and (11) implementing a no-show protocol. Progress is being monitored with daily management reports. These procedures help maintain participant contact even for controls and information about whether a phone is lost, stolen, or damaged. Data collected at assessments are identified by study ID, not participant name. The form linking study IDs to names and the data themselves are kept in GAINS ABS, a secure electronic data management system.

### Sample size

For the primary outcome (H1) power analysis, we assumed a sample size of 400 with treatment intake records/services data from the provider (for covariates), interviews by research staff at three time points for the main analysis (baseline and 3 and 6 months), a completion rate of 90 + % per wave of 100 participants, a moderate effect size of Cohen’s *d* = .4 based on Cox’s formula [71] for converting the odds ratio from a pilot study to effect size *d* = LN(1.9)/1.65 = .4)), a target of at least 90% power with a family wise alpha of < .017 on the three a-priori orthogonal contrasts testing the hypothesized effects of EMA, EMI, and their interaction on the primary outcome (days of abstinence), and at least 80% power for all six pairwise comparisons with a family wise alpha of < .0083. The effective *n* for power calculations in repeated measures analysis varies between a lower bound of the number of unique people (*N* = 400 people) and an upper bound of observations from baseline and completed follow-up or 1120 observations (O = (400 people + 90% × 400 people × 2 follow-ups) = 1120) as a function of the Intraclass Correlation Coefficient (ICC) associated with the individual and the number of repeated measures (RM) per person (effective *n*’ = O/(1 + ICC(RM − 1)). In prior samples from the proposed recruitment site [6], the ICC of the days of abstinence between enrollment, 3, and 6 months post enrollment was .52, resulting in an effective *n*’ of 549 (*n*’ = 1120/(1 + .52(3 − 1)) = 549) and 98% power for a two-tailed test of *p* < .017. Note that in the special case of a balanced 2 × 2 as proposed here, the power for the interaction test is the same as each of the main effects [71–74]. In the same study, the ICC of the HIV Risk Behavior Scale was .51, resulting in an effective *n*’ of 554 and 99% power for a two-tailed test of alpha < .05. For the six possible pairwise comparisons, the effective sample size (*n*’ = 275 per pair for H1 and H2) will be sufficient to have 80% power for a two-tailed test of *p* < .0083. Following the recommendations of Piantadosi [75], we have powered this design for the most conservative pairwise tests so that we can look at the efficacy of each combination (EMA, EMI, EMA + EMI) relative to the control and their comparative effectiveness with each other. For mediation analysis (H3), the tests should have 90% + power for a two-tailed test of *p* < .05 for an indirect effect size of *d* = .22 or more.

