### Statistical analysis

#### Missing data

Participants complete their intake and enrollment interviews before randomization. Based on past experience, we expect to complete 90% or more of the 3- and 6-month post-enrollment interviews and have less than 1% missing data on core items. Multiple imputations will be used to replace missing data to allow the least biased estimate for each analysis [76]. To further reduce potential bias, analyses will be rechecked by running them without missing data. If differences result, a general latent variable framework [77] will be used to analyze non-ignorable or systematic missingness that tests whether missing data are qualitatively different by condition.

#### Analysis for aims 1 and 2

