We will evaluate the effects of EMAs, EMIs, and EMAs + EMIs on the days of abstinence (H1) and HIV risk behaviors (H2) measured from enrollment to 6 months after enrollment using multilevel structural equation modeling (MSEM) with mixed effects in MPlus (version 6.1). The analysis will model observations (level 1) nested within participants (level 2), with participants modeled as a random factor. Random assignment to the four groups will be modeled as a level 2 predictor in the 2 × 2 factorial design [78] with the three planned orthogonal contrasts shown earlier in Table 1. To be conservative, a Bonferroni correction for family wise error (*p* = 05/3 = 0.017) will be used on primary outcome (days of abstinence) in the three a-priori hypothesis tests for the effect of getting EMA or not (H1a), EMI or not (H1b), and their interaction (H1c). As noted earlier, self-monitoring via EMAs is expected to change behavior. Based on the preliminary studies, we expect EMIs to have an effect in their own right and for the combined EMA + EMI condition to have an additional effect (i.e., an interaction). This and all analyses will use an intent-to-treat approach (i.e., participants are analyzed as assigned regardless of their actual level of participation). Prerandomization participant characteristics, severity, and treatment experience used for urn randomization will be checked for any group differences and used in a propensity score covariate to further reduce unexplained variance. Restricted maximum likelihood estimation (REML) will be used within condition to allow the use of all available data. If there is a significant effect for H1 or H2, we will also examine all six of the possible pairwise comparisons, using an experiment-wise error of .05 and a pairwise test alpha of .05/6 tests = .0083.

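### The effective sample size of 549 counts 400 pre-randomization interviews as outcome observations; the follow-up waves give 474, and the 80% pairwise power claim fails

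*Protocol article*

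**What the plan says.** The Sample size section starts from 400 people and names "interviews by research staff at three time points for the main analysis (baseline and 3 and 6 months") as the data for the main analysis. For the effective n it sets "an upper bound of observations from baseline and completed follow-up or 1120 observations". It counts these observations as "400 people + 90% × 400 people × 2 follow-ups", which is 1120, and deflates them by 1 + ICC(RM − 1) with RM = 3. The correlation used is described so: "the ICC of the days of abstinence between enrollment, 3, and 6 months post enrollment was .52". This gives 549 for days of abstinence and, with an ICC of .51, 554 for the HIV Risk Behavior Scale. The section sets d = .4, a target of at least 90% power at .017 for the three contrasts (98% claimed), and 80% power at .0083 for the six pairwise comparisons with 275 per pair. It adds that the design was powered for the pairwise tests.

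The Missing data section states that enrollment interviews precede randomization, and the recruitment section gives the same order. H1 concerns abstinence in the 6 months after discharge. Under Analysis for aims 1 and 2, outcomes are "measured from enrollment to 6 months after enrollment using multilevel structural equation modeling", with observations at level 1 and participants at level 2. On the treatment term it says: "Random assignment to the four groups will be modeled as a level 2 predictor".

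**The concern.** The formula O/(1 + ICC(RM − 1)) gives the effective n for a group difference that is present at every wave counted. At the enrollment interview the expected group difference is zero by design. Counting that wave in O and RM, and then applying the full d = .4 to the result, credits the trial with information about the treatment effect that those 400 interviews do not hold when used this way. They can help as a covariate, but that is a different calculation.

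Two things are at stake. First, the stated effective n and the powers that rest on it, above all the pairwise power, because H1 and H2 are worded as comparisons with the control group. Second, the same three-wave thinking may carry into the primary model. If it does, and the group term is a main effect over all waves, the tested coefficient averages a true effect with a null one.

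**Working it through.** **Inputs (protocol article, Sample size, unless noted).** N = 400; two follow-up waves at 90% completion (also in Missing data: "we expect to complete 90% or more of the 3- and 6-month post-enrollment interviews"); ICC .52 (abstinence) and .51 (HIV risk); d = .4, which unrounded is ln(1.9)/1.65 = .389; two-sided alpha .017 (contrasts) and .0083 (pairs).

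**Power formula.** For two equal halves of an effective n (written n'), the noncentrality is d√n'/2. Power is approximately Φ(d√n'/2 − z), with z = 2.387 at .017 and 2.640 at .0083. I also ran the noncentral t. The contrasts are taken as the plan treats them, with one d and one n' for each.

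**1. The plan's own figures.**
- O = 400 + .9 × 400 × 2 = 1120. n' = 1120/(1 + .52 × 2) = 1120/2.04 = 549. This reproduces.
- HIV risk: 1120/2.02 = 554. This reproduces.
- Contrast power at .017: .4 × √549/2 = 4.69, so 98.9% (98.5% with d = .389), against 98% stated. This reproduces.
- HIV risk at .05: 99.7%, against 99% stated. This reproduces.
- Pairwise, n' = 275 at .0083: .4 × √275/2 = 3.32, so 75.1% by the normal approximation and 74.4% by noncentral t (72.1% and 71.4% with d = .389). The stated 80% does **not** reproduce, even with baseline counted.

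**2. Follow-up waves only, same formula.** O = 720, RM = 2.
- Abstinence: n' = 720/1.52 = 473.7. The stated 549 is 16% higher (549/473.7 = 1.16).
- HIV risk: n' = 720/1.51 = 476.8.

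| Test | n' | d = .40, normal (t) | d = .389, normal (t) | Stated |
|---|---|---|---|---|
| H1 contrast, .017 | 474 | 97.5% (97.5%) | 96.8% (96.7%) | 98% |
| H2, .05 | 477 | 99.2% (99.2%) | 98.9% (98.9%) | 99% |
| H1 pair, .0083 | 237 | 66.9% (66.1%) | 63.8% (63.0%) | 80% |

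**3. Conditional case: baseline in the outcome vector, group main effect only.** The expected coefficient is about .4 × 720/1120 = .257, a reduction of 1 − 720/1120 = 35.7%. With n' = 549, contrast power at .017 is 73.4% (70.6% with d = .389), and pairwise power at .0083 with n' = 275 is about 31% (29%). A simulation of this model (random intercept with ICC .52, wave effects, no effect at baseline, 10% missing per follow-up wave, 400 replicates) gave a mean estimate of .251 and 72% contrast power.

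**4. Models that avoid the dilution.** Assume an equal correlation of .52 between all three waves and 360 people with both follow-ups.
- Enrollment value as covariate: variance of the follow-up mean = (1 + .52)/2 − .52² = .4896, so effective n = 360/.4896 = 735. Contrast power is above 99%; pairwise power is 88% (86% with d = .389).
- Change from baseline (a pre/post group-by-time contrast): variance = .76 + 1 − 1.04 = .72, so effective n = 360/.72 = 500. Contrast power is 98%; pairwise power is about 70% (67%).

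**The case against.** The best defense is that the count barely matters for the primary contrasts. Power is about 97% at 474. It is still about 95% (93% with d = .389) at the plan's own lower bound of 400 people, and about 92% (90%) at 360. With full baseline adjustment, 549 would be conservative. All of this stands, and it confines the damage to the stated figures and the pairwise claim. It does not make 549 right, because the plan derives that number from three outcome waves, not from covariate adjustment. It is also fair that the pairwise shortfall is partly a separate error, since 275 does not give 80% either.

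A reader might go further and infer that the primary analysis, as written, shrinks the effect by 36%. The documents do not establish that. The outcome period named under Analysis for aims 1 and 2 is also covered by the 3- and 6-month interviews, each of which looks back 90 days. A level 2 predictor only has to vary between persons and may act on slopes as well as on the intercept. The urn variables, which include pretreatment abstinence and HIV risk, enter through a propensity score covariate; that is not full adjustment for the enrollment value, but it does use earlier outcome information as a covariate. The finer model specification may sit in an analysis plan that is not shown, so the absence of a group-by-time term from a condensed article is not itself a fault.

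On the other side, the Sample size section lists baseline among the main-analysis time points while naming provider intake records as the source of covariates ("we assumed a sample size of 400 with treatment intake records/services data from the provider"), and its formula treats all waves alike. The diluted reading is therefore supported but not fixed.

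**Conclusion.** The effective sizes of 549 and 554 do not apply to a post-randomization effect. On the plan's own formula and inputs they should be 474 and 477. Contrast power falls by one to two points, to about 97%, and still meets the 90% target. Pairwise power is about 63–66% by noncentral t, against 80% stated. Of that gap, the plan's own 275 already accounts for the fall to about 71–74%, and removing baseline accounts for the rest. The range in each case runs from d = .389 to d = .40.

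The dilution to about .257 SD, with contrast power of about 73% and the 90% target missed, holds only if baseline is an outcome wave under a group main effect with no group-by-time term or baseline constraint. It is a risk to be closed off in the text, not an established bias. The figure of 735 rests on an equal correlation of .52 across all waves and on 360 people with both follow-ups. The plan gives one overall ICC and does not show that the enrollment-to-follow-up correlation equals the one between follow-ups.

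**What to change.** In Analysis for aims 1 and 2, state that the tested quantity is the group difference over the 3- and 6-month values. Analyze those values with the enrollment value as a covariate. Alternatively, keep three waves with the group effect constrained to zero at baseline, or with a group-by-time contrast that isolates the follow-up difference.

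In Sample size, replace 1120, 549 and 554 by 720, 474 and 477, and restate contrast power as about 97% and pairwise power as about 63–66%. If the covariate model is adopted, an effective n of about 735 with pairwise power of about 86–88% may be quoted beside these, but only with its two assumptions written out. Otherwise withdraw the statement that the design is powered for the pairwise tests.

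The cost is wording in the protocol and analysis plan and a few restated numbers. No participants, visits or measures are added, because the enrollment value is already collected. The model should be fixed before outcomes are examined by group; the article reports 343 of 400 enrolled at 28 February 2017.

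### The 98% power extended to the EMA × EMI interaction needs a difference-of-differences of about 0.8 SD, which does not fit the plan's own hypotheses; at 0.4 SD it is about 48%

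*Protocol article*

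**What the plan says.** The Sample size section takes one effect size, obtained by "converting the odds ratio from a pilot study to effect size *d* = LN(1.9)/1.65 = .4". It applies this to "three a-priori orthogonal contrasts testing the hypothesized effects of EMA, EMI, and their interaction on the primary outcome", with "a target of at least 90% power with a family wise alpha of < .017". The repeated-measures adjustment is given as "resulting in an effective *n*’ of 549", leading to "98% power for a two-tailed test of *p* < .017". The section then notes that, because the 2 × 2 is balanced, "the power for the interaction test is the same as each of the main effects". It gives no separate size for the interaction. It also claims 80% power for all six pairwise comparisons, which include each single component against control.

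Two other places describe the expected pattern. Aims and hypotheses (H1) predicts more abstinent days than control in the EMA, EMI and EMA + EMI arms. Analysis for aims 1 and 2 makes the interaction the test of H1c and says "we expect EMIs to have an effect in their own right and for the combined EMA + EMI condition to have an additional effect", which is a positive interaction.

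**The concern.** Balance makes the three contrasts orthogonal and gives them equal standard errors when they are scaled alike. It does not make the three effects equally large, and power depends on both. Carrying 98% over to the interaction therefore assumes an interaction size that is never stated, and that size is hard to square with the expected pattern of arm effects.

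The interaction is one of three confirmatory tests of the primary outcome. The Background (using EMA responses to prompt EMI use) names combining EMAs with EMIs as the trial's primary goal. If the interaction test has roughly even odds where the plan implies near-certainty, readers have the wrong basis for weighing a non-significant result.

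**Working it through.** **Inputs (Sample size section, except allocation).** d = .4; n' = 549 in total; two-sided alpha .017, so z = 2.387; target power 90%; 25% allocation per condition (Randomization section).

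**Step 1: reproduce the plan's figure.**
- n' = 1120/(1 + .52 × 2) = 549.
- SE of a main effect = 2/√549 = .085 SD.
- Power = Φ(.4 × √549/2 − 2.387) = Φ(4.686 − 2.387) = 98.9%.
- With the unrounded d = ln(1.9)/1.65 = .389, power is 98.5%. The stated 98% is reproduced for a main effect.

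**Step 2: put the interaction on the scale of arm differences.** Set control = 0, EMA-only = a, EMI-only = b and EMA + EMI = c.
- DoD = c − a − b. The orthogonal interaction contrast, scaled like a main effect, is DoD/2.
- With n'/4 per cell, SE(DoD) = √(16/549) = .171 SD, twice that of a main effect.
- Equal power therefore needs a DoD twice the main effect: .8 SD for d = .4 (.78 for the unrounded d; about .76 for exactly 98.0%).

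**Step 3: solve for the arm means.** The EMA main effect is (c + a − b)/2 = a + DoD/2, and the EMI main effect is b + DoD/2. With both at .4 SD, a = b = .4 − DoD/2 and c = a + b + DoD = .8 SD. Interaction power is Φ(DoD/.171 − 2.387).

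| DoD (SD) | Interaction contrast (SD) | Each single arm minus control (SD) | EMA + EMI minus control (SD) | Interaction power |
|---|---|---|---|---|
| .8 | .4 | 0 | .8 | 98.9% |
| .63 | .31 | .09 | .8 | 90% |
| .6 | .3 | .1 | .8 | 87% |
| .4 | .2 | .2 | .8 | 48% |
| .2 | .1 | .3 | .8 | 11% |
| 0 | 0 | .4 | .8 | 1.7% (alpha) |

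The 90% row comes from (2.387 + 1.282) × 4/√549 = .63. Every row keeps both main effects at .4 SD and so keeps the 98% for those two tests. Only the interaction power and the single-arm effects change, and they move in opposite directions.

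**Step 4: compare with the plan's own text.** The row that delivers the stated power has no effect of either component alone. H1 predicts such effects against control, Analysis for aims 1 and 2 expects one for EMIs, and the pairwise power claim presupposes differences to detect. With main effects of .4 SD, a single-component effect of .4 SD leaves a DoD of zero.

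**Step 5: sensitivity to n'.** The plan's lower bound is 400 people. At n' = 400, a DoD of .4 SD has about 35% power.

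**The case against.** The strongest reply is that the sentence is not an arithmetic error. For equally scaled orthogonal contrasts of equal size in a balanced 2 × 2 it is correct, and the plan does speak of orthogonal contrasts. This stands. The fault is that equality is presented as following from balance, without the condition on effect size.

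Second, a design effect is often a detectable size for each test taken separately, not a joint prediction. This also stands in part. A reader might infer that the plan assumes single arms equal to control; it does not say so and gives no arm means. That result follows only when both main effects are set to +.4 SD together with a positive interaction of the same contrast size. A DoD of −.8 SD would have the same two-sided power, with all three active arms at .8 SD, but the plan expects the combination to add something.

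Third, a reader might infer that H1a and H1b are contradicted. As tested in Analysis for aims 1 and 2 they are main effects, and both stay at .4 SD throughout. The conflict is with the versus-control form in Aims and hypotheses. Nor should the zero difference between EMA-only and EMI-only be blamed on the interaction assumption: it follows from equal main effects alone. Only the two comparisons of a single component with control are affected.

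Fourth, a DoD of .4 SD is an illustration chosen here, not a figure from the plan. That is why the full range is shown.

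Finally, nothing in the article says that a non-significant interaction will be read as no added effect. The six pairwise comparisons give another view of the combination, though only after a significant effect for H1 or H2. The risk of misreading is a reason to state the power correctly; it is not something the plan commits to.

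**Conclusion.** The point holds as a power statement that lacks its condition. The 98% is sound for the main effects. It carries over to the interaction only for a DoD of about .8 SD, and with main effects of .4 SD and a positive interaction that leaves no room for EMA-only or EMI-only to beat control. In the example with single arms at +.2 SD and the combination at +.8 SD, which agrees in direction with every stated hypothesis, interaction power is about 48%, well short of the 90% target. That target needs a DoD of about .63 SD.

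These figures rest on the plan's own n' = 549, equal allocation, a common SD, the normal approximation and both main effects at .4 SD. The tests, the alpha and the sample size are not in question.

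**What to change.** Replace the sentence on interaction power with: *Power for the interaction equals that for the main effects only if the interaction contrast is also .4 SD (difference-of-differences .8 SD); for a difference-of-differences of .4 SD it is about 48%, and 90% power requires about .63 SD.* Report the estimated DoD with its confidence interval, so that a non-significant interaction is not taken as evidence of no added effect.

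No extra participants are needed and no analysis changes. Trial status puts enrolment at 343 of the planned 400 on 28 February 2017, and the change can be made at any stage. Its only cost is a less favourable stated power for the interaction.

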### Randomization

Participants are randomly assigned to receive recovery support as usual (control), EMAs only, EMIs only, or combined EMAs + EMIs. Randomization uses urn randomization [62] with a base rate of 25% per condition stratified by participant characteristics (gender, race, age, recruitment cohort, level of comfort using a smartphone), pretreatment measures of the dependent variables (days of abstinence, HIV risk behaviors), and prerandomization treatment (level of care, length of stay, type of discharge) to increase the likelihood that participants are distributed similarly across conditions. Urn randomization adjusts the probability of assignment to a condition in ways that simultaneously minimize differences in multiple stratification variables [63, 64]. Only the research coordinator and protocol monitor responsible for scheduling, proficiency testing, and protocol supervision have access to information about who is in each condition. The research coordinator informs participants of their group assignment, describes the next steps, schedules training, and provides an appointment card for the next office visit.

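### The stated 80% power for each pairwise comparison does not follow from the plan's own inputs, which give about 75%

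*Protocol article*

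**What the plan says.** The Sample size section of the protocol article sets two power targets under one assumed effect, d = .4. The first is at least 90% for the three factorial contrasts at .017. The second is "at least 80% power for all six pairwise comparisons with a family wise alpha of < .0083".

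The section builds an effective sample size from "O = (400 people + 90% × 400 people × 2 follow-ups) = 1120" observations and a repeated-measures deflation, noting that "the ICC of the days of abstinence between enrollment, 3, and 6 months post enrollment was .52". This gives 549 in total, which it halves to "275 per pair for H1 and H2". It concludes that this "will be sufficient to have 80% power for a two-tailed test of" p < .0083, and adds that "we have powered this design for the most conservative pairwise tests".

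The section on analysis for aims 1 and 2 confirms the threshold as "a pairwise test alpha of .05/6 tests = .0083". It runs the six pairwise comparisons only if H1 or H2 shows a significant effect. The Randomization section gives a "base rate of 25% per condition", so the two arms of any pair are equal in size.

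**The concern.** Effect size, effective sample size, alpha, sidedness and power are all printed in one paragraph, so the last should follow from the other four. It does not.

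The figure matters for two reasons. The plan offers the pairwise tests as the basis on which the design was powered. Also, Aims and hypotheses words H1a to H1c as each active arm against control, whereas the planned primary tests are factorial contrasts (EMA or not, EMI or not, interaction). Direct arm-versus-control tests occur only among the six pairwise comparisons. On the plan's own inputs, the chance of missing a true pairwise difference of d = .4 is about 25%, not 20%, so a null pairwise result would be read with somewhat more confidence than the calculation supports.

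**Working it through.** **Inputs (Sample size section unless noted)**
- d = .4, from LN(1.9)/1.65 = .389, rounded.
- Effective n' = 275 per pair, so 137.5 per arm (equal allocation, Randomization section).
- Two-tailed alpha .0083, that is .05/6 (analysis for aims 1 and 2).
- Observations O = 1120, ICC = .52 (days of abstinence) or .51 (HIV risk), 3 waves.

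**Step 1: reproduce the plan's other figures.** The plan's formula is n' = O/(1 + ICC(RM − 1)).
- Abstinence: 1120/(1 + .52 × 2) = 1120/2.04 = 549, as stated.
- HIV risk: 1120/(1 + .51 × 2) = 1120/2.02 = 554, as stated.

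Power for two equal groups with total effective size n' is Φ(d√n'/2 − z), where z is the 1 − alpha/2 normal quantile.
- Main contrasts, n' = 549, alpha .017: 98.9% at d = .4 and 98.5% at d = .389. Stated: 98%.
- H2, n' = 554, alpha .05: 99.7% at d = .4. Stated: 99%.

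The method is therefore consistent with the plan's own.

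**Step 2: the pairwise figure by the same method.**
- z for .05/6, two-tailed = 2.638.
- d√n'/2 = .4 × √275/2 = 3.317.
- Power = Φ(3.317 − 2.638) = Φ(.679) = 75.1%. Noncentral t: 74.4%.
- With d = .389: 72.1%.
- With n' = 277 (half of 554, for H2) and d = .4: 75.5%.

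Stated: 80%.

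**Step 3: what 80% would need.**
- At d = .4: n' = 4(2.638 + .842)²/.16 = about 303 per pair.
- At n' = 275: d = (2.638 + .842) × √(4/275) = about .42.

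**Step 4: could another reading give 80%?**
- One-sided .0083: 79.7% (d = .389) or 82.2% (d = .4). The text says two-tailed.
- Two-sided .017: 79.9% (d = .389) or 82.4% (d = .4). The text says .0083.
- 275 read as per arm: 98.0%.

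Either of the first two may be where the 80% came from, but that is a guess; the article does not say.

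**Step 5: conditional sensitivity to the use of baseline.** The plan counts the enrollment interview as one of three outcome waves, although the Missing data section says it precedes randomization.
- Two follow-up waves only, unadjusted: O = 2 × 360 = 720; n' = 720/1.52 = 473.7, or 236.8 per pair; power 66.9% (d = .4) or 63.8% (d = .389).
- Mean of the two follow-ups, directly adjusted for baseline, assuming every between-wave correlation is .52 and 90 completers per arm: variance = (1 + .52)/2 − .52² = .4896; 90/.4896 = 183.8 per arm, 367.6 per pair; power 88.4% (d = .4) or 86.2% (d = .389).

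Neither case is the analysis the article describes.

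**The case against.** The strongest reply is that a lower figure in a planning formula does not make the design underpowered. That stands. A reader might infer that the design misses its own 80% target, or that its true power is 67%. The documents support neither. The 67% requires baseline to be discarded and the follow-ups analyzed unadjusted, and the article plans no such thing: pretreatment days of abstinence is an urn variable, and the urn variables enter the model through a propensity score covariate. That is weaker than direct adjustment, but it is not discarding baseline. Equally, the 86% to 88% cannot be used to defend the stated 80%. It rests on an assumed common correlation and on an adjustment the article does not specify, and the 80% was claimed for n' = 275.

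Two further readings should not be pressed. Writing .389 as .4 is rounding to one decimal, so the 72% is a sensitivity value and not a second error. And power for all six comparisons beside a per-test alpha ordinarily means that each comparison has that power if its own difference is d = .4; it is not a claim that all six differences equal .4 at once.

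It can also be said that the article expects 90% completion or more. Full completion (O = 1200) raises power to 78.5% (ICC .52) or 79.0% (ICC .51) at d = .4, which is still below 80% and gives n' of 588 or 594 where the plan prints 549 and 554.

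Finally, the pairwise tests are follow-ups, run only after a significant H1 or H2 result. This lowers the weight of the point. It does not remove it, since the plan itself says the design was powered on these tests.

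**Conclusion.** The stated 80% is wrong as written. The plan's own formula and inputs give about 75% per pairwise comparison (74.4% by noncentral t; 72% with d unrounded), a shortfall of about 5 points, or 8 with d = .389. This conclusion uses only printed inputs and a method that agrees closely with the neighboring figures.

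What is shown is an incorrect power statement, not an underpowered trial. The primary factorial contrasts, at the plan's assumed d, are unaffected: about 99% as planned, and 97.5% even if the two follow-up waves alone are counted (n' = 473.7, alpha .017, d = .4), against a target of 90%. No estimate, alpha level or decision rule changes. The point is a reporting correction of moderate weight.

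**What to change.** In the Sample size section, replace the pairwise figure with *about 75% power per pairwise comparison at d = .4 (80% at d of about .42)*. Amend the target of at least 80% for the pairwise comparisons, and the sentence saying the design was powered for them, to agree.

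A higher figure of about 86% to 88% may be quoted only if direct adjustment for baseline days of abstinence is specified in the analysis, and the assumptions behind it (all between-wave correlations equal to .52, 90 completers per arm) are stated beside it.

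The cost is one restated figure and two amended statements, with no change in sample size. The Trial status section reports 343 participants enrolled by 28 February 2017, so the correction should be in place before pairwise results are interpreted.
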